## **Abstract**

**Introduction.** The birth plan is the written report of the mother preferences about the management of his childbirth in topics where choices are available because of safety and effectiveness. Birth plans may help to the pregnant women in reaching real expectations about her childbirth, improve her involvement on decision makings, increasing the control on the birth process and reaching a satisfying experience.

## **Objectives**

To evaluate the effectiveness of a counselling intervention in the birth plan, based on “shared decision-making”, in pregnant women in relation to the presentation of the birth plan to the hospital and on preferences regarding aspects related to childbirth and satisfaction with the childbirth, compared to the standard counselling.

To evaluate the effectiveness of a counselling intervention in the birth plan, based on “shared decision-making”, in pregnant women in relation to the degree of information received in the pregnancy about the childbirth, with respect to the standard counselling

**Design.** A cluster randomised trial study, multicentre, parallel which will reveal the effectiveness of counselling intervention birth plan will be held based on "shared decision-making".

**Participants:** Pregnant women with prenatal care in Sexual and Reproductive Health Care (ASSIR) centres and who wish to participate in the study. Sample size: 266 pregnant women will be studied, 133 in each of the groups.

**Statistical analysis:** Descriptive analysis will be performed in all the variables and a bivariant analysis through hypothesis testing. Confidence interval CI will be settled on 95%. A multivariate analysis, relative risks with a CI of 95%.

**Keywords:** birth plan, assessment, midwives, satisfaction, shared decision making.

## **BACKGROUND AND CURRENT STATUS OF THE TOPIC**

The experience of the birth of a child is an important event in a woman's life. The birth plan is the written expression of the mother's preferences regarding the management of her childbirth in those aspects in which there are equally effective and safe alternatives . Its main purpose is to promote decision-making not influenced by the emotions that arise during the birth process and to provide a vehicle for communication between future parents, the care provider and the hospital team . In addition, it helps the pregnant woman to understand her personal values, needs and concerns in the birth process . Its preparation can help the pregnant woman to have real expectations of childbirth, involve her in decision-making, thus increasing control over the birth process and have a satisfactory experience with the birth experience . This document is used to express knowledge of your rights and duties as a user, to be responsible for your health, your legal capacity to consent or not to certain procedures and also ask that your decisions be respected as stated in Spanish Law 41 / 2002 on the autonomy of the patient established in art. 4.1 .

The competence framework of the gynaecological obstetric nursing specialty (midwives) includes the care of low and medium risk pregnancy and childbirth, and in its midwives must support pregnant women in the preparation of the birth plan . This needs to be approached, by midwives, with strategies that allow future parents to complete it . According to Epstein et al, clinical decision-making should be taken from the creation of a collaborative relationship with the patient and family using the best available evidence, consistent with the patient's values, objectives and capacities . The use of tools to help patients make decisions regarding routine practice improves the perception of the probabilities of the results, the congruence between the chosen option and the person's values .

The available literature on the usefulness and satisfaction of birth plans is scarce and inconclusive. A retrospective study carried out in Murcia revealed that only 2.6% of pregnant women presented the birth plan document to the hospital, and significant differences were also found in the increase in skin-to-skin contact, in delayed clamping of the umbilical cord, in the increase in spontaneous vaginal birth and in the decrease in hospital stay in women who used the birth plan . In a study with qualitative methodology carried out in Mexico, all women showed satisfaction with the experience of completing the birth plan even though their experience did not fully conform to what

was specified in the birth plan. The mere fact of writing down their preferences was valued as a more personal and rewarding experience . A clinical trial in Taiwan on the birth plan found significant differences in relation to the fulfilment of the expectations of the women in the experimental group that showed an increase in control over the birth process, as well as greater satisfaction in it . In contrast, in an experimental study carried out in Sweden, they did not find that carrying out the birth plan improved the birth experience; although it could have beneficial effects in relation to fear of childbirth and pain in women .

The bibliography also highlights the different points of view that health professionals have on birth plans, in some studies they describe them as useful since they highlight the preferences of women, improve communication with pregnant women and address the concerns of these . On the other hand, other studies define that the term "birth plan" can be misleading and create false expectations and put pressure on midwives and the multidisciplinary team .

In Spain in 2007, the National Health System drew up the "Strategy for Attention to Normal Childbirth" to respond to the demand of women to actively participate in their childbirth  and in the same year in Catalonia, the Catalan Health Institute published the "Protocol for the natural assistance of normal childbirth" , and both documents include the "birth plan".

Within the portfolio of services of the Sexual and Reproductive Health Care (ASSIR) in Primary Care in Catalonia, midwives carry out the control and monitoring of pregnancy and postpartum of low and medium risk pregnant women in health centres  and the birth of women is attended in the reference hospitals.

In 2016, a survey carried out in Catalonia on the satisfaction of women in care in the maternity process showed that the degree of global satisfaction with the care received was high, 8.30 out of 10. However, women report that 67.2%, 64.2%, and 57.6% received sufficient information on pregnancy, birth and postpartum respectively .

The professionals of the ASSIR and the reference Hospitals jointly developed the birth plan with the aim of allowing women to actively participate in decision-making, and to be a communication instrument that favours the transmission of the wishes of women between primary care and hospital. However, the level of implementation of the birth plan is not known since neither in ASSIR nor in obstetric areas of hospitals is there a record on its presentation and use. In the bibliographic review carried out, not enough

evidence was found of the effectiveness of the advice given by midwives on the birth plan to pregnant women. That is why studies are needed to verify whether standardized counselling in the completion of the birth plan, or counselling based on “shared decision-making”, influences the presentation of birth plans to the hospitals, women’s preferences on aspects of childbirth, satisfaction with the information received and satisfaction with childbirth.

## **HYPOTHESIS**

- Counselling on the birth plan for pregnant women, based on "shared decision making" will increase the presentation of birth plans to the hospital.
- Counselling on the birth plan for pregnant women, based on “shared decision-making” will modify: preferences on aspects related to childbirth, the degree of satisfaction with the information received in the pregnancy on the childbirth and the degree satisfaction in childbirth, in relation to the pregnant women who receive the usual counselling

## **OBJECTIVES**

### **Main objectives**

To evaluate the effectiveness of a counselling intervention in the birth plan, based on “shared decision-making”, in pregnant women in relation to the presentation of the birth plan to the hospital, the preferences regarding aspects related to childbirth and satisfaction with the childbirth, compared to the standard counselling.

To evaluate the effectiveness of a counselling intervention in the birth plan, based on “shared decision-making”, in pregnant women in relation to the information received during the pregnancy about the childbirth, with respect standard counselling.

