### **Secondary objectives**

- 1.- Describe the pregnant women's sociodemographic and obstetrics characteristics.
- 2.- Analyse if there are differences between the pregnant women of both study groups in the preferences regarding: companion, physical space, delivery procedures, pain relief methods, second stage of birth, the baby and breastfeeding.
- 3.-Find out the perception of pregnant women on the degree of usefulness of the preparation of the birth plan.
- 4.- To find out the degree of global satisfaction of pregnant women in childbirth, satisfaction in decision-making in first and second stage childbirth in pregnant women in both study groups.

5.-Determine the reasons for non-presentation of the birth plans to the hospitals of the pregnant women in both study groups.

6. Find out if there are differences, according to the sociodemographic and obstetric characteristics of the pregnant women, in the presentation of birth plans to the hospital, in the preferences of aspects related to childbirth, the degree of information received in the pregnancy about the childbirth and in satisfaction in childbirth in both study groups.

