## **Subjects**

Target population Pregnant women with prenatal care in the health care centres of the ASSIR from Catalonia

Inclusion criteria. Older pregnant women with prenatal care in the centres study, with childbirth in the reference hospitals, who wish to participate in the study and want to fill in the birth plan

Exclusion criteria. Illiteracy, language barrier, drug addiction, alcoholism, grade 2, 3 and 4 heart disease, severe associated maternal pathology, type I-II diabetes, uterine malformation, diagnosed foetal malformation, threatened preterm birth, twin or multiple pregnancy, cervical incompetence, previous perinatal death, intrauterine growth retardation, placenta previa, isoimmunization, mild-severe preeclampsia, premature rupture of membranes, maternal infection.

Sample size. The sample calculation has been made based on the main variable of the study “presentation of birth plans”. Based on the descriptive pilot study (n = 211 pregnant women), 48% of the women who receive the usual advice presented the

birth plan to the hospital. It is estimated that this prevalence may be higher in women who receive counselling, around 68%. In this study, a randomized, multicentre and parallel experimental design in clusters is proposed (4 ASSIRs participate). Applying an alpha error of 5%, a beta error of 20% and taking into account the influence of the clusters in the analysis, a total of 133 are required in the control group and 133 in the intervention group. 15% loss to follow-up has been estimated. The calculation has been carried out using the macros of SPSS V22. An interim analysis will be performed to assess whether the sample size needs to be recalculated so that there is sufficient power for the subgroup analysis.

Sampling technique. In the random assignment of ASSIR, the characteristics of the reference hospitals will be taken into account, since they have different levels of care. Thus, two ASSIRs will be assigned to the intervention group and two to the control. For this assignment, the Epidat 4.1 program will be used. This type of assignment has been chosen to avoid contamination among midwives who will or will not receive specific training on birth plan counselling based on shared decision making.

The sampling technique of pregnant women within each ASSIR will be consecutive and proportional to the number of first visits (see table 1).

Table 1. Proportional sampling according to the number of first ASSIR visits

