### **Analysis.**

A descriptive analysis of all variables will be carried out. The categorial ones with frequencies and percentages; the quantitative ones with mean and standard deviation and if they do not comply with a normal distribution, the median, minimum, and maximum will be observed. The statistical software package SPSS 22.0 will be used. Homogeneity tests between the groups will be performed for the main sociodemographic variables to analyse the comparability of the groups. Hypothesis contrast tests, Chi-square test and Student's t test will be performed. A statistical significance level of 5% will be used. Confidence level will be settled on 95%. A multivariate analysis, relative risks and number of subjects will be calculated with a confidence interval of 95%.

**Bibliographic search.** The databases consulted for the search were MEDLINE; Cochrane; EBSCO; CINAHL and CUIDEN from 2000 to 2016 Keywords: birth plans, assessment, midwife, satisfaction, decision making.

**Ethical aspects.** The principles of the Declaration of Helsinki  will be considered and the necessary precautions will be taken to minimize the possible repercussions on pregnant women during the investigation according to the recommendations of the Belmont report.  Authorization will be requested from the Committee on Clinical research ethics of the Jordi Gol i Gorina Foundation for the ASSIR of the Catalan Institute of Health. The information sheet and informed consent is common for participants in the control and intervention group. Throughout the process, the confidentiality of the data will be guaranteed according to Organic Law 15/1999, on the protection of confidential data .

**Difficulties and limitations.** Women can also access birth plan information through other pregnant women or other means such as the internet that could modify decisions regarding it. To avoid contamination among midwives in the counselling

activity, a randomization of ASSIR has been chosen. The possible losses that may be due to a change in the risk of gestation after 29 weeks that limit following the completed birth plan and/or require a childbirth in a hospital other than that of reference. In situations where neonatal death occurs, the degree of satisfaction will not be evaluated.

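### The main objectives list four unranked outcome families, two of which reappear as secondary, while the sample size rests on one main variable; presentation of the birth plan should be named sole primary outcome throughout

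*Protocol*

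**What the plan says.** - **Main objectives (Protocol).** The first names "the presentation of the birth plan to the hospital, the preferences regarding aspects related to childbirth and satisfaction with the childbirth". The second assesses the intervention "in relation to the information received during the pregnancy about the childbirth, with respect standard counselling". That makes four outcome families with no order among them. The objectives in the Abstract list the same four.
- **Secondary objectives.** Item 2 reads "Analyse if there are differences between the pregnant women of both study groups in the preferences regarding" and goes on to the sections of the birth plan. Item 4 covers overall satisfaction with childbirth and satisfaction with decision-making. Two of the four main families are therefore also secondary.
- **Subjects, sample size.** "The sample calculation has been made based on the main variable of the study", in the singular, and that variable is presentation of birth plans.
- **Hypothesis.** Presentation has its own statement, with a direction (an increase). Preferences, information and satisfaction share a second statement, which says only that they will change.
- **Outcome variables.** Preferences are given as a list of yes/no items with no summary score. No variable in these lists is labelled primary.
- **Analysis.** Chi-square and t tests are planned, and "A statistical significance level of 5% will be used", without reference to a particular outcome.

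**The concern.** A reader who starts from the objectives finds four main outcomes. A reader who starts from the sample size finds one. A reader of the secondary objectives finds that two of the four are not main at all. These statements have to be reconciled before results are known, because they lead to different conclusions if, say, presentation shows no difference but a few preference items do.

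Preferences make this more acute. They are many separate items, and the hypothesis names neither an item nor a direction for them. Under the main objectives as worded, nothing prevents a shift in some items, either way, from being reported as bearing on a main objective. The 5% error rate would then no longer describe the trial's main claim.

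**Working it through.** **1. The plan's own figure.** The inputs in the sample-size paragraph are "48% of the women who receive the usual advice presented" the plan, "women who receive counselling, around 68" per cent expected with the intervention, and "Applying an alpha error of 5%, a beta error of 20" per cent. A two-sided test is assumed, since sidedness is not stated. With pooled variance:

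n = [1.960·√(2·0.58·0.42) + 0.842·√(0.48·0.52 + 0.68·0.32)]² / 0.20² ≈ 94.4, so 95 per arm.

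Allowing for 15% loss, 95/0.85 gives 112. The stated 133 per arm implies a design effect of 133·0.85/95 = 1.19 if loss is included, or 133/95 = 1.40 if it is not. No intracluster correlation or design effect is given, so 133 is attainable but cannot be checked. What matters here is that the calculation uses one outcome at the full 5%.

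**2. Count of tests.** This is our count from the Outcome variables list, not a figure in the protocol. Preference items: companion 1, space 2, comfort 2, fluids 1, monitoring 2, movement 1, pain relief 6, birth 4, baby 5, total 24. Adding presentation, total satisfaction score and information gives 27. The two decision-making subscales make 29, and change of preferences makes 30.

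**3. Chance of at least one false positive, independent tests at 5% and no true effects.** The formula is 1 − 0.95^k.

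| k | What is tested | Chance |
|---|---|---|
| 4 | one test per family | 18.5% |
| 27 | 24 items + 3 | 75.0% |
| 29 | plus two subscales | 77.4% |
| 30 | plus change of preferences | 78.5% |

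For k = 27 the expected number of false positives is 27·0.05 = 1.35.

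**4. Allowing for correlation.** The documents give no correlations, so a range is assumed. Simulated normal test statistics with a common correlation (200,000 draws, two-sided 5%) give:

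| Common correlation | 27 tests | 4 tests |
|---|---|---|
| 0.1 | 73% | 18% |
| 0.3 | 63% | 17% |
| 0.5 | 48% | 16% |
| 0.7 | 32% | 13% |

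**5. What keeping several primaries would cost.** Using the presentation rates and a Bonferroni split, since no effect sizes are given for the other families:

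- Four families at 0.05/4 = 0.0125: 135 per arm before loss and clustering, against 95 (135/95 = 1.42).
- All 27 tests at 0.05/27 = 0.00185: 189 per arm (189/95 = 1.99).

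The 135 already exceeds the planned 133 before loss and clustering are added. With presentation alone at 5%, the planned 266 stands.

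**The case against.** The strongest reply is that the protocol does signal a hierarchy. The sample-size paragraph names a main variable, and the hypothesis puts presentation first, on its own and with a direction. Powering a trial on one variable while stating several main objectives is not in itself a contradiction. A multiplicity procedure can also be left to a statistical analysis plan, which is not shown here. Much of this stands. It shows what the sponsor probably intended, and the lack of an adjustment method is not part of this point. It does not remove the inconsistency: the objectives do not carry the designation, and two families are labelled both main and secondary. Those labels belong to the protocol.

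Several stronger readings are tempting but not supported:

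- **That the trial could claim success on almost any result.** The 75% is the chance of at least one false positive among 27 independent tests with no true effects; it is not a probability of success whatever happens. Independence is also implausible. Continuous and intermittent monitoring, directed and spontaneous pushing, and labour without anaesthesia and epidural are plainly related, although women may tick more than one option.
- **That no outcome is marked as decisive.** The sample-size paragraph does mark one; the objectives do not follow it.
- **That one significant preference item meets a main objective.** The protocol states no such criterion. The main objectives name preferences as a single topic, and the itemised comparison appears under secondary objective 2.
- **That clustering adds to these error rates.** Clustering is a separate issue. The figures above assume each test is valid at 5%.

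**Conclusion.** The point holds as an inconsistency about which outcome is primary: four unranked main families, two of them also secondary, and a sample size for one. Its size depends on how the main objectives are read. If every family can support a claim of effectiveness, the false-positive chance is about 18.5% with one independent test each (13% to 18% under the correlations tried). With every preference item tested it is about 75% under independence, or roughly 32% to 73% for common correlations of 0.7 to 0.1. All of these exceed 5%. They rest on our count of 27 tests (up to 30), on no true effects, and on tests that are each valid at 5%. If presentation alone decides, as the sample-size paragraph suggests, the main claim stays at 5%; the protocol needs to say so consistently. This should be corrected. The remedy is a matter of wording and does not require a redesign.

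**What to change.** Name presentation of the birth plan to the hospital (yes/no) as the sole primary outcome in the Abstract, Hypothesis, Main objectives and Analysis, matching the sample-size paragraph. List the satisfaction total score, sufficient information and preferences as secondary only, each in one place. State that preference items alone cannot support a claim of effectiveness. How the items are handled beyond that, for example as exploratory estimates with intervals or as a Holm-adjusted family, can be left to the statistical analysis plan.

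The cost is that fewer outcomes can be called main. The sample size of 266 and the data collection are unchanged, and the main claim is held at 5% provided the test of presentation is itself valid.

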### **Secondary objectives**

- 1.- Describe the pregnant women's sociodemographic and obstetrics characteristics.
- 2.- Analyse if there are differences between the pregnant women of both study groups in the preferences regarding: companion, physical space, delivery procedures, pain relief methods, second stage of birth, the baby and breastfeeding.
- 3.-Find out the perception of pregnant women on the degree of usefulness of the preparation of the birth plan.
- 4.- To find out the degree of global satisfaction of pregnant women in childbirth, satisfaction in decision-making in first and second stage childbirth in pregnant women in both study groups.

5.-Determine the reasons for non-presentation of the birth plans to the hospitals of the pregnant women in both study groups.

6. Find out if there are differences, according to the sociodemographic and obstetric characteristics of the pregnant women, in the presentation of birth plans to the hospital, in the preferences of aspects related to childbirth, the degree of information received in the pregnancy about the childbirth and in satisfaction in childbirth in both study groups.

